### Methods for additional analyses (e.g., subgroup analyses) {20b}

No subgroup analyses on the outcomes are planned, though suspension or premature discontinuation and closure of the study may occur if the participation in study procedures poses unexpected, significant, or unacceptable risk, as described in section {22} addressing adverse events.

### Interim analyses {21b}

No interim analyses on the outcomes are planned.

### Methods in analysis to handle protocol non-adherence and any statistical methods to handle missing data {20c}

We will report any differences in consent, withdrawal, and loss-to-follow-up by randomization arm. We do not have plans for imputation for missing data.

### Plans to give access to the full protocol, participant-level data, and statistical code {31c}

Access to a cleaned, deidentified dataset and code may be requested after the study is completed and accompanying manuscripts are published. The primary aim is a study-wide analysis and will be disseminated as such. Any publications and presentations prior to the release of the primary results will not impede the integrity of those results.

## Oversight and monitoring

### Composition of the coordinating center and trial steering committee {5d}

The principal investigators will serve as study monitors. They will ensure compliance with the investigational plan as well as IRB regulations, hosting weekly study team meetings focusing on progress monitoring and safeguarding against unanticipated problems. Protocol deviations will be discussed in weekly review meetings and corrective actions will be identified. Furthermore, the principal investigators will be notified of serious adverse events within 24 h and non-serious adverse events within 7 days and follow-up to resolution.

Quality assurance measures will also be implemented to ensure protocol compliance and data quality. During training of study personnel, detailed review and feedback will be provided regarding informed consent procedures. Reliability checks will be implemented on a routine basis for the administration of clinical outcome measures, with a minimum of 20% reviewed. Research assistants will be trained to enter and review data quality in REDCap. Data from REDCap will be downloaded regularly as an excel file to a secure drive and inspected for accuracy and completeness. Furthermore, a representative sample of source data from the case report form will be checked against the REDCap study database to ensure accurate entry. A data manager will also review REDCap data for plausibility and completeness and will flag and follow up on potential errors.

### Composition of the data monitoring committee, its role, and reporting structure {21a}

Independent oversight of study safety will be conducted by the Data Safety Monitoring Board (DSMB). The DSMB is responsible for monitoring and minimizing study risks, reviewing modifications to risk management protocols, monitoring enrollment progress, and recommending study continuation based on ongoing risk versus benefit analysis. The DSMB will receive biannual reports summarizing safety and enrollment data as well as any revisions to the study protocol. The DSMB will also be notified within 24 h of any serious adverse events.

### Adverse events reporting and harms {22}

Adverse events will be monitored by study staff from the treatment baseline through the final study visit. Participants will be advised during the consenting process to notify study staff immediately if they experience any new or unusual side effects during participation. Upon initiation of treatment, weekly check-ins will be completed to inquire about potential adverse events. Non-leading questions will be asked (e.g., “How have things been going for you? How has your mood been? How have you felt physically? Have you noticed anything different in the past week?”). Participants will be provided weekly handouts on potential adverse side effects associated with estradiol treatment. Serious adverse events, as defined by the FDA, will be reported to the principal investigators and the Data Safety Monitoring Board (DSMB) within 24 h, to the university IRB within 5 days of occurrence, and, for unexpected serious adverse events, to the study sponsor within ten business days. Other adverse events that are non-serious, but deemed study related, will be reported biannually to the DSMB.

Ongoing trial safety monitoring, compliance, and progress will be conducted by the principal investigators, the DSMB, and the sponsor. The DSMB will convene biannually, or sooner if required (e.g., in the case of serious adverse events), to formally evaluate the progress and safety of the trial. The following circumstances may warrant suspension or premature discontinuation and closure of the study:Participation in study procedures poses unexpected, significant, or unacceptable risk (e.g., three or more serious adverse events reported).There are findings of (a) insufficient compliance with the study protocol, (b) data are not sufficiently complete or evaluable, or (c) trial progress is determined insufficient.There has been a clear demonstration of trial (a) efficacy or (b) futility.

In the case of premature termination or suspension, the principal investigators will inform the study participants, the IRB, and the study sponsor, citing the specific reason(s) for the suspension/termination decision. In the case of suspension, the study may resume when concerns are determined to be adequately addressed.

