### Eligibility criteria {10}

The study will include unmedicated, perimenopausal outpatient women ages 44–55 who are in late perimenopause and experiencing anhedonia and/or psychosis symptoms with onset coinciding with perimenopausal menstrual irregularity. To determine participant eligibility, women will undergo initial online and phone screening, the structured clinical interview for the DSM-5 (SCID-5), laboratory testing, and a pelvic exam/PAP test (or a medical records review for an exam within 3 years). Participants must meet the following inclusion criteria to be enrolled in the study:44–55 years old, unmedicated, naturally perimenopausal woman in stage −1 of the Stages of Reproductive Aging Workshop (STRAW) criteria [36, 37]At least mild perimenopausal-onset anhedonia (SHAPS≥20) (Snaith et al. [38])Absent-to-moderate perimenopausal-onset psychosis spectrum symptoms as measured by the Brief Psychiatric Rating Scale (BPRS-Positive Symptom Subscale Score between 6 and 17) (Hafkenscheid [39]; Overall & Gorham [40])

Dimensional measures of anhedonia and psychosis severity are used to stratify participants. With respect to stratification, equal numbers of participants will be recruited into each of the following four strata:Mild-to-moderate anhedonia + absent-to-mild psychosisMild-to-moderate anhedonia + moderate psychosisHigh anhedonia + absent-to-mild psychosisHigh anhedonia + moderate psychosis

Mild–moderate anhedonia severity is defined in this trial as Snaith–Hamilton Pleasure Scale (SHAPS [38]) scores between 20 and 36, and high anhedonia severity is defined as SHAPS>36 (using the ordinal scoring of Franken et al. [41]). There is no widely accepted clinical cut-off on the SHAPS, though a meta-analysis by Trøstheim and colleagues (2020) [42] reported that caseness is indicated by scoring more than 1.96 SDs above the general population, which would correspond to a SHAPS score of 25 or greater (see also Alsayednasser and colleagues [43]). However, in this trial, a SHAPS score cutoff of >20 was used to indicate at least mild, clinically impairing anhedonia, consistent with the cutoff used in the NIMH Fast-Fail Trial for Mood and Anxiety Disorders [38, 44]. The SHAPS has shown adequate psychometric properties in clinical and non-clinical samples [45], and ROC analyses suggest that a SHAPS score of ≥ 20 corresponds to clinically significant anhedonia from a general population sample [38].

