### Procedure for unblinding if needed {17b}

Participants will be unblinded at the end of treatment/outcome data collection, at which point active treatment participants will commence 1 week of progesterone (200 mg/day, Prometrium® oral capsules, or its generic) combined with an additional week of estradiol (0.1mg/day, Climara® patch, or its generic) to stimulate menstruation and reduce the risk of endometrial hyperplasia.

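### The rule for passing non-serious adverse events to the DSMB depends on a case-by-case relatedness judgement, which is a poor filter in perimenopausal women and is not aligned with the DSMB reporting section

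*Protocol article*

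**What the plan says.** Collection is broad. Section {22} states: "Adverse events will be monitored by study staff from the treatment baseline through the final study visit". It adds: "Upon initiation of treatment, weekly check-ins will be completed to inquire about potential adverse events". Neither sentence asks whether an event is related to the study.

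Reporting upward is less uniform:

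- **To the principal investigators**, section {5d} gives a deadline for "non-serious adverse events within 7 days and follow-up to resolution". There is no relatedness condition.
- **To the DSMB, serious events** go within 24 h under sections {21a} and {22}. Again there is no relatedness condition.
- **To the DSMB, non-serious events** are covered by one specific sentence in section {22}: "Other adverse events that are non-serious, but deemed study related, will be reported biannually to the DSMB".
- **To the DSMB, in general**, section {21a} says: "The DSMB will receive biannual reports summarizing safety and enrollment data as well as any revisions to the study protocol". It does not define the safety data, and it does not say whether they are shown by arm.

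Two further passages matter. Section {10} enrols women "experiencing anhedonia and/or psychosis symptoms with onset coinciding with perimenopausal menstrual irregularity". Section {17a} keeps study personnel blind except for the study coordinator who blinds and administers the treatment. The article does not say who judges relatedness or by what criteria.

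**The concern.** The relatedness filter sits at one step only, between the study team and the independent board, and it applies only to non-serious events. A case-level causality opinion is weakest where the background condition looks like the drug effect. Every participant is in late perimenopause, and her symptoms began alongside menstrual irregularity. An unexpected bleed on estradiol can reasonably be put down to perimenopause, one woman at a time, and each such decision removes an event from what section {22} sends on. The protocol treats this area as relevant to safety: undiagnosed vaginal bleeding is an exclusion, and section {17b} gives progesterone after treatment "to stimulate menstruation and reduce the risk of endometrial hyperplasia".

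A randomised placebo arm makes the opinion unnecessary. If all events are counted by arm, background bleeding appears in both columns and an excess on estradiol appears as a difference. Section {21a} makes the DSMB responsible for recommending continuation on a risk-benefit review. No interim outcome analyses are planned (section {21b}), so the safety report is a main source for that review.

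**Working it through.** The plan gives no figure for this point, so the main check sets the passages side by side.

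1. **Is there a filter?** The same non-serious events have no relatedness condition at collection ({22}) or on the way to the principal investigators ({5d}). The condition appears only in the sentence on DSMB reporting ({22}).
2. **Does another section remove it?** Section {21a} could be read as covering all safety data, but it names no content. If it means all events, the sentence in {22} is misleading. If {22} governs, the board sees a filtered set. The two sections need reconciling either way.
3. **Is the filter reliable here?** For bleeding, no: it overlaps with the entry condition in {10}, and no outcome measure named in the article is described as recording it. Mood differs. SHAPS and BPRS are taken at baseline, weeks 1 and 2 and end of treatment ({18a}) and modelled by treatment group ({20a}). Depression, anxiety and climacteric scales are also collected.
4. **Could the filter differ by arm?** Section {17a} leaves the study coordinator unblinded. If that person contributes to relatedness judgements, the filter could act differently in the two arms. The article neither says nor excludes this.

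**Illustration only.** The bleeding rates and filter fractions below are assumptions, not figures from the article. Take 50 women per arm (100 enrolled, equal allocation assumed), with true rates of 10% on placebo and 30% on estradiol: 50 × 0.10 = 5 and 50 × 0.30 = 15 women. If a fraction f is called unrelated in both arms, the visible counts are 5(1 − f) and 15(1 − f), and the visible difference is 20(1 − f) percentage points. The last column is the chance that the visible counts show an estradiol excess at two-sided Fisher p < 0.05, from exact binomial enumeration.

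| f | Placebo | Estradiol | Difference (points) | Chance of p < 0.05 |
|---|---|---|---|---|
| 0 | 5 | 15 | 20 | 64% |
| 0.3 | 3.5 | 10.5 | 14 | 41% |
| 0.7 | 1.5 | 4.5 | 6 | 9% |
| 0.9 | 0.5 | 1.5 | 2 | under 1% |

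An equal filter leaves the ratio at 3 to 1, so it thins the signal without distorting it. An unequal filter distorts it. With f = 0.7 on estradiol and 0.3 on placebo, the visible counts are 15 × 0.3 = 4.5 and 5 × 0.7 = 3.5, a difference of 1/50 = 2 points. With the fractions reversed they are 15 × 0.7 = 10.5 and 5 × 0.3 = 1.5, a difference of 9/50 = 18 points.

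The table uses full enrolment. For most of the trial a biannual report would hold fewer women.

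**The case against.** The strongest reply is that section {22} does not say other events are withheld, and that section {21a} already promises the DSMB a safety summary with no relatedness condition. On that view the board may receive everything and only the wording needs tidying. Part of this stands: the article does not prove that unrelated events are kept from the board. But the only sentence that specifies which non-serious events go to the DSMB carries the condition, and a team following it literally would apply it.

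A reader might go further and infer that estradiol effects resembling perimenopause will never be compared between arms. The documents do not support that. All events are collected and reach the principal investigators, nothing bars a table by arm, and the final safety analysis may sit in a full protocol or analysis plan that is not shown. A reader might also infer that worsening mood would be lost. It largely would not be, given the scales collected in both arms.

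Two other objections hold. The direction of any misjudgement is not established: section {22} also provides weekly handouts on estradiol side effects, which could lead to events being called related in either arm. And an undivided table by arm would mislead, because after unblinding only the estradiol arm receives progesterone plus a further week of estradiol (treatment arms section and {17b}), and this is intended to bring on menstruation. The article does not say whether the final study visit, where event monitoring ends, falls before or after that week.

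Finally, serious events reach the board within 24 h whatever their relatedness, which limits what is at stake.

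**Conclusion.** The point holds for DSMB monitoring of non-serious harms during the trial, and no further. As section {22} is written, the board's view of those harms depends on a relatedness judgement with no stated assessor or criteria, in a population where bleeding in particular is hard to attribute. Section {21a} is too general to settle whether the board sees more.

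The size cannot be derived from the document. The illustration shows only that, under assumed rates, a threefold excess could become hard to see even when both arms are filtered equally. The primary mechanistic endpoints are not affected. The change is worth making because it is cheap and improves the information on which the board judges risk against benefit.

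**What to change.** Reword the sentence in section {22} so that all non-serious adverse events are tabulated by arm in the biannual DSMB report, whatever their judged relatedness, with relatedness as an additional column. Align section {21a} by stating that its safety summary contains this table. Have the arm supplied through the IDS, which holds the randomisation list (section {16c}), so that the blinded study team stays blinded. Show events in the 3-week randomised period separately from events in the week after unblinding. State who judges relatedness and whether the unblinded coordinator takes part.

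The cost is a few sentences and a longer table that includes background events, against which the placebo column gives the comparison. No new data are collected, and no dose, treatment or stopping rule changes.

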### Frequency and plans for auditing trial conduct {23}

Internal audits of this trial are conducted quarterly. Intervention implementation and quality improvement are addressed at weekly team meetings with the study PIs, co-investigators, and study staff.

### Plans for communicating important protocol amendments to relevant parties (e.g., trial participants, ethical committees) {25}

Changes to the study protocol must be approved by the IRB and reported to the study sponsor. Furthermore, any modifications to risk management protocols will be approved by the DSMB. If significant deviations from the existing study protocol occur, they will be reported to the IRB within 2 weeks as well as in annual progress reports to the sponsor and to the DSMB during their biannual meeting schedule, or within 4 weeks for serious violations (e.g., confidentiality breach). We used the SPIRIT Checklist to assist with presenting this protocol.

## Dissemination plans {31a}

In accordance with NIH sponsor policy, the results and accomplishments of study activities will be made publicly available. All peer-reviewed manuscripts will be submitted to the public-access PubMed Central digital archive upon acceptance for publication. Every attempt will be made to publish the clinical trial results in peer-reviewed journals. Furthermore, upon completion of the clinical trial, study data will be deidentified and the archived data will be shared publicly on the NIMH Data Archive (NDA). In accordance with the NIH policy on the Dissemination of NIH-Funded Clinical Trial Information and the Clinical Trials Registration and Results Information Submission rule, the clinical trial will be registered at ClinicalTrials.gov and results of the study will be submitted to this website.

## Discussion

Affective and psychotic conditions show increased prevalence during the perimenopause compared to pre- and postmenopausal periods [3, 4]. While fluctuations in ovarian hormones, in particular estradiol, are thought to trigger the onset of perimenopausal affective [7] or psychotic symptoms [5], not all women show susceptibility. Furthermore, estrogen treatment shows empirical support for reducing perimenopausal affective [8–10] and psychosis symptoms [5]; however, benefits are not universal. Characterizing neuromolecular pathways by which estrogen fluctuations during the perimenopausal period (e.g., via ovarian quiescence or estrogen treatment) trigger affective and psychotic symptoms is warranted. The mesolimbic dopamine pathway shows dysfunction in both depression [20, 21] and psychosis [24, 25]. Furthermore, fluctuations in estradiol have been found to alter the function in this pathway [26]. Preclinical evidence suggests the mesolimbic dopamine pathway may mediate the relationship between ovarian hormone withdrawal and depressive symptoms [12]. The PEEPS study will be the first mechanistic clinical trial to probe the relationship between neural and molecular measures of reward system function and estrogen-mediated changes in affective and psychosis behaviors during the perimenopausal period. The results of this trial will inform future studies predicting susceptibility to perimenopausal affective and psychotic conditions and developing targeted treatments.

In accordance with the NIMH RDoC framework, this trial aims to characterize the etiology of psychiatric symptoms experienced during the perimenopausal period in terms of varying degrees of impairment in psychological and biological systems linked to Positive Valence System dysfunction [66]. Specifically, this mechanistic trial will use transdiagnostic inclusion criteria measuring psychiatric symptom dimensions (i.e., anhedonia, psychosis) linked to both the perimenopausal transition and dysfunction in brain reward system functioning. In complement and with the intent of increasing sample homogeneity, the trial will use DSM-based criteria to exclude participants who present with conditions linked to reward system dysfunction with non-endocrine-related etiology. By applying this integrated RDoC framework with DSM-based exclusion criteria in a pharmacologic, simultaneous PET-fMRI design, this study may serve as a framework for probing the neuromolecular basis by which specific pharmacologic compounds impact broad psychological domains implicated in mental health and well-being. In the context of reproductive transitions and associated mental health symptoms, this paradigm could be modified to address the effects of various sex hormones on neurotransmitter systems to characterize susceptibility and evaluate treatments. Such research has the potential to broadly enhance scientific understanding of relationships between sex hormones, neurotransmitter system function, and psychiatric symptom dimensions in women across hormone transitions, including puberty, menstruation, pregnancy, and menopause.

## Trial status

This trial was granted UNC-Chapel Hill Institutional Review Board approval on 12/16/2021 and approval by its Data Safety Monitoring Board in April 2022. Recruitment was initiated on 04/01/2022. This is version 1.6 of the study protocol (06/09/2022). Recruitment will end December 31, 2026.

## Data Availability

Upon completion of the study, the data will be made available for download from the NIMH National Database Archive (NDA), collection #4215.

## Abbreviations

PEEPs: Perimenopausal Effects of Estradiol on Anhedonia and Psychosis Study
BPRS: Brief Psychiatric Rating Scale
RDoC: Research Domain Criteria
BOLD: Blood oxygen level dependent
MID: Monetary incentive delay
SCID-5: Structured Clinical Interview for the DSM-5
STRAW: Stages of Reproductive Aging Workshop
SHAPS: Snaith–Hamilton Pleasure Scale
BMI: Body mass index
